#### Shift level measures and primary outcome

Our performance outcome of interest is subject compliance with text message assessments. Our primary intervention outcome of interest is self-reported fatigue at the end of scheduled shifts. Single-item measurement is the preferred approach for research that involves real-time data capture and/or ecological momentary assessment (EMA) [39,40]. We based the construction of our single-item outcome measure and the scale for respondents to record their subjective response on prior EMA research of insomnia [41]. We hypothesize that study subjects in the intervention group will report lower levels of fatigue at the end of shift than study subjects in the control group.

#### Follow-up measures

Each study subject will complete the following survey assessment tools at 90 days: the PSQI, CFQ, SAS, OFER, and SFAB.

#### Sample size

In planning the study, several unknowns prevented a well-informed sample size analysis including the number of shifts each participant would contribute and the amount of correlation in fatigue between multiple shifts within the same subject. We assumed that compliance would be high for all study subjects, with over 80% of text message assessments answered [42]. Due to the pilot nature of the study, we conservatively assumed a minimum of one observation per person and then determined the number we would need to see a large effect size for the ‘proof-of-concept’ outcome. Based on our previous cross-sectional data [15,16] we assumed that 50% of EMS workers would report fatigue at the beginning of or during shift (at risk population). If N = 25 per study arm, we will have 80% power to detect a large effect size of 0.78 difference in the mean end of shift fatigue score between control and intervention groups (alpha = 0.05), using a two-sample Mann-Whitney U test power analysis (PASS software, NCSS Statistical Software, Kaysville, Utah, United States) assuming the actual distribution is logistic. Given the 50% expected rate of fatigue at baseline, we will recruit and randomize 100 participants (50 per group) to obtain the ‘at risk’ number needed within each arm.

#### Statistical analysis

We will describe overall number of shifts per provider and the mobile text participation for all study subjects. For example, we will quantify compliance with our text message queries and the number that were lost to attrition. We will use linear mixed-model analyses to examine the effectiveness of the intervention on reducing reported fatigue at the end of shift among all participants and among only those reporting fatigue at baseline. We will construct a model where the outcome is the reported fatigue at the end of each shift, a fixed effect for experimental group, a fixed effect of time in study, and a random effect for subjects to account for multiple shifts within each person. We will examine the estimated change in fatigue score per shift in the intervention group compared to the control group. Post-estimation testing will be used to describe the correlation in fatigue scores within the subjects across shifts. The same methodology will be used to analyze end of shift sleepiness and difficulty in concentrating.

The eight scale components of the SFAB survey are measured at baseline and at the end of the study. Likert responses will be scored as continuous measures and weighted from 0 to 100, with higher scores indicating more positive scores. We will test for changes over time and between-group differences in these scales using one sample and two sample t-tests, assuming the underlying distribution of the outcomes are normal. If the data are highly skewed we will use non-parametric tests including the sign rank test and Mann-Whitney U test. All statistical testing will be two-sided with alpha set at <0.05 using STATA version 10 SE (StataCorp LLP, College Station, Texas, United States) and SAS version 9.2 (SAS Institute Inc., Cary, North Carolina, United States).

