### Recruitment protocol

After an emergency worker views the website an appointment for telephone screening and enrollment is made via email by the emergency worker. If eligible, subjects complete the following steps: 1) text the words ‘Sleep Track TXT’ to the study telephone number to register his or her cell or smartphone with the SMS system; 2) visit the study portal webpage and watch the informed consent video and make a selection to voluntarily participate or not (this is at time of enrollment); 3) if the subject agrees to participate, he/she will create a unique login and password; 3) the subject will then login and answer baseline survey questions that capture demographics and patterns of sleep, fatigue, and shiftwork; 4) the subject will then use a calendar tool to register his or her shift schedule for the next 90 days. Subjects can use the calendar tool to add or edit shifts at any time during the study. Consenting subjects will answer baseline survey questions and provide the contact information of at least one contact if needed for follow-up. This study has been approved by the University of Pittsburgh Institutional Review Board (IRB number: PRO13120428).

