### Measures

#### Participant level measures

After completion of the informed consent process we will collect demographic data on age, sex, alcohol consumption, smoking status, perceived general health, employment status, and eight other demographic factors. Other baseline measures will include sleep quality, fatigue, attitudes about shift scheduling, and perceptions of work-related fatigue and recovery (see Table 1). Sleep quality will be measured with the widely used and reliable Pittsburgh Sleep Quality Index (PSQI) [35]. A PSQI score of 6 or more on a 21-point scale indicates poor sleep quality [35]. Mental and physical fatigue at work will be measured using the Chalder Fatigue Questionnaire (CFQ) [36]. The CFQ is an 11-item scale of mental and physical fatigue that has been used in multiple emergency worker populations and shown by psychometric testing to be reliable and valid [15,16]. A CFQ score exceeding one of two scoring benchmarks can indicate severe mental and physical fatigue. Attitudes about shift scheduling will be measured with the Schedule Attitudes Survey (SAS) [37]. The SAS is a 21-item scale that measures a worker’s attitudes about his or her shift schedule. The tool’s intended use was for schedule modification and design by employers. The SAS has been used in diverse populations, including EMS workers, and is shown to have positive psychometric properties of reliability and construct validity [20]. Higher scores on the SAS are interpreted as representing greater dissatisfaction towards one’s current shift schedule.

**Table 1 T1:** Schedule of measurements for the study in SleepTrackTXT pilot trial

**Measure**	**At baseline enrollment**	**Beginning of every scheduled shift**	**Every 4 hrs during scheduled shifts**	**End of every scheduled shift**	**Subject reports an injury (at end of shift, or at any time)**	**At 90-days end of study**
Demographic survey	X					
Pittsburgh Sleep Quality Index (PSQI)	X					X
Chalder Fatigue Questionnaire (CFQ)	X					X
Schedule Attitudes Survey (SAS)	X					X
Occupational Fatigue, Exhaustion, Recovery Scale (OFER)	X					X
Sleep, Fatigue, Alertness Behavior Survey (SFAB)	X					X
Hours of sleep in past 24 hours		X				
Rate sleepiness now		X	X	X		
Rate fatigue now		X	X	X		
How difficult is it to concentrate now		X	X	X		
Estimate total number of patients you saw during your shift				X		
Were you injured during your shift?				X	X	
Describe the type of injury and body part affected*				X*	X*	

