## Discussion

The SleepTrackTXT pilot trial could provide evidence of compliance and effectiveness that would support rapid, widespread expansion in one of two forms: 1) a stand-alone program in the form of a tailored/individualized worker sleep monitoring and fatigue reduction support service; or 2) an add-on to a multicomponent fatigue risk management program led and maintained by employers or by safety and risk management services.

Our study design has several strengths. We will characterize the performance of an SMS tool for the purpose of assessing sleep and fatigue in real-time among a highly vulnerable shift worker population. We will provide a detailed picture of variability in sleepiness and fatigue over the course of shiftwork and expose moments of greatest need for intervention. This is significant given that the existing literature, especially involving the prehospital emergency medical services clinicians, is largely limited to cross-sectional study designs [43]. These cross-sectional data may be misrepresented as typical of an emergency clinician’s state of sleepiness or fatigue over the entirety of a shift, no matter shift length or volume of work. Existing interventions or agency level policies based on cross-sectional data may be misinformed and ineffective. Capturing variability in a clinician’s condition over the course of an 8, 12, 16, 24-hour or longer shift schedule exposes points in time more proximal to when a subject may be at greatest risk of a negative outcome and the opportunity when an intervention may realize its greatest impact and benefit.

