These data will offer preliminary answers to common questions such as: how severe are sleepiness and fatigue at the end of a 24 hour shift versus a shift of shorter length? The main methodological challenge will be subject compliance with text message assessments occurring during the shift period at intervals of every four hours. Many clinicians will be busy with patient care or other activities and find it difficult to respond. Study subjects working longer shifts (for example a 24 hour shift) will be set to receive many more text messages than subjects working shifts of a shorter length. Text messages may be perceived as repetitive and there is limited human contact with the study team. The ideal number of text messages per shift or per day is unknown. One study reports study subjects’ perceived ideal total number of daily text messages is 5.5 (range 1 to 20) [46]. Attrition over time is another challenge. Recent studies involving SMS-based assessments and interventions report attrition or withdrawal rates of 2.4 to 3.2% [46,47]. Studies of sensitive subjects such as sexually transmitted disease report lower longterm adherence and compliance and higher attrition [48]. Sleep and fatigue are highly visible topics within the EMS industry that are controversial when the topic of shift length restriction is discussed [43]. This is the first study of its kind and it is unclear if the noted controversy related to shift length restriction would impact recruitment or attrition. We have included a modest incentive program to address the threat of attrition. We have included an end of shift question about participant workload, which will be used in the analysis as a stratification variable for different levels of compliance with scheduled queries during shiftwork.

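### The end-of-shift fatigue model leaves out the enrolment fatigue score that the trial already collects, which gives up some precision but causes no bias

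*Protocol article*

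**What the plan says.** The section on shift level measures names the outcome: "Our primary intervention outcome of interest is self-reported fatigue at the end of scheduled shifts". It is a single-item rating sent by text message.

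The Statistical analysis section then gives the model: "We will construct a model where the outcome is the reported fatigue at the end of each shift", followed by "a fixed effect for experimental group, a fixed effect of time in study, and a random effect for subjects to account for multiple shifts". No other covariate is named for this outcome anywhere in the article. Fatigue at baseline appears once in the analysis, to define who is included: the model is run "among all participants and among only those reporting fatigue at baseline". Workload is also named, in the Discussion, but for a different purpose: "which will be used in the analysis as a stratification variable for different levels of compliance with scheduled queries during shiftwork".

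Two candidate covariates are already collected. Table 1 schedules the CFQ, an 11-item scale of mental and physical fatigue, at enrolment and at 90 days for all subjects. Under Recruitment protocol, "the subject will then use a calendar tool to register his or her shift schedule for the next 90 days", and shifts may be added or edited later. The Discussion speaks of following clinicians "over the course of an 8, 12, 16, 24-hour or longer shift schedule".

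**The concern.** A random subject effect accounts for the fact that some people are habitually more fatigued than others, but it does not remove that variation from the comparison of the arms. Group is a subject-level factor. Once each person contributes many shifts, the standard error of the group difference is governed almost entirely by how much subjects differ from one another. A subject-level baseline measure related to the outcome reduces exactly that component.

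The trial randomises 50 per arm and is powered on 25 at-risk subjects per arm for a large effect only. Randomisation restricts the imbalance in group size and names no stratification factor. What is at stake is the width of the interval for the main effectiveness estimate.

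**Working it through.** **1. The plan's own figure.** Inputs from the Sample size section: 25 per arm, effect size 0.78 (read as SD units), alpha 0.05, Mann-Whitney test, logistic distribution, one observation per person. Two-sided testing comes from Statistical analysis. The relative efficiency of the Mann-Whitney test to the t-test for a logistic distribution is π²/9 = 1.097. A noncentral-t calculation with 25 × 1.097 = 27.4 per arm gives 80.9% power. Equivalently, the t-test needs 27 per arm, and 27 / 1.097 = 24.6, so 25. A simulation of the Mann-Whitney test on logistic data gave 78.9%. The stated 80% is reproduced, and it assumes no covariate.

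**2. Formula.** Set the total variance to 1, let ICC be the between-subject share, m the shifts per subject, and r the correlation of enrolment CFQ with a subject's underlying mean fatigue.

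- Variance of a subject mean, unadjusted: ICC + (1 − ICC)/m
- Adjusted for CFQ: ICC(1 − r²) + (1 − ICC)/m
- Detectable difference at 80% power, n per arm: (1.96 + 0.84) × √(2 × variance / n)

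The article says that the number of shifts and the within-subject correlation are unknown, and it gives no r. All three are assumptions here.

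**3. Limit for many shifts.** Only ICC(1 − r²) matters.

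- r = 0.3: between-subject variance down 9%; SE factor √0.91 = 0.954, so about 5% lower.
- r = 0.5: variance down 25%; SE factor √0.75 = 0.866, so about 13% lower.

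**4. A worked case: ICC 0.5, m = 20, n = 50 per arm.**

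| | Variance of a subject mean | SE reduction | Detectable difference |
|---|---|---|---|
| Unadjusted | 0.5 + 0.025 = 0.525 | – | 0.41 SD |
| r = 0.3 | 0.455 + 0.025 = 0.480 | 4.4% | 0.39 SD |
| r = 0.5 | 0.375 + 0.025 = 0.400 | 12.7% | 0.35 SD |

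The last row is worth 0.525/0.400 − 1 = 31% more participants; the row above it, 0.525/0.480 − 1 = 9%. With ICC from 0.3 to 0.7 and 20 or 40 shifts, the SE reduction at r = 0.5 stays between 11.9% and 13.2%.

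**5. With one observation per person** (the plan's sizing basis) the gain is smaller. At ICC 0.5 the variance falls from 1 to 0.955 (r = 0.3) or 0.875 (r = 0.5), so the SE falls by 2.3% or 6.5%.

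**6. Shift length as a second covariate.** Suppose it explains 20% of within-subject variance. In the worked case with r = 0.5 the variance becomes 0.375 + 0.020 = 0.395, and the SE reduction moves from 12.7% to 13.3%. If shift length also explains a further 10% of between-subject variance, the variance is 0.325 + 0.020 = 0.345 and the reduction is 19%. So it matters for the mean contrast mainly if people differ in their usual shift length.

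**7. If the target is a slope.** The section also says that the per-shift change in fatigue score will be compared between the groups, although the listed terms contain no group-by-time interaction. Under a random intercept, a slope contrast depends on within-subject variation. Enrolment CFQ then adds almost nothing. Shift length explaining 20% of within-subject variance would lower the SE by 1 − √0.8 = 11%.

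**The case against.** The strongest reply is that nothing here is wrong. The unadjusted randomised comparison is valid, the power statement holds, and in the worked case the mixed model already detects 0.41 SD without adjustment, well inside the 0.78 target. An article may also leave covariate lists to an analysis plan that is not shown. The first part stands in full. The last carries less weight, because this article does state the model's terms.

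A reader might infer that the omission biases the result or leaves the trial underpowered. The documents support neither. Chance imbalance in baseline fatigue is already reflected in the unadjusted interval. The plan meets its own 80% without adjustment.

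A reader might also infer that baseline fatigue and shift length together dominate the variance, so that adjustment would be worth half as many subjects again. No correlation is given to support that. CFQ is a different instrument from the single-item outcome, so the correlation may be modest, and it will have a restricted range in the subset already fatigued at baseline. The range of shift lengths comes from a general remark in the Discussion, not from a description of the sample.

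Timing deserves care. The Randomization section places allocation at the first login attempt, and Recruitment protocol places the baseline survey after the login is created, so CFQ may formally follow allocation. It still precedes every shift message and so cannot carry an effect of the recommendations. Start-of-shift ratings do follow randomisation, later ones may carry the intervention effect, and any may be missing: the Sample size section assumes only that more than 80% of assessments are answered.

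**Conclusion.** The point holds as lost efficiency. The listed model uses baseline fatigue only to choose a subset, while a suitable enrolment score is collected from all subjects. For the group difference in mean end-of-shift fatigue, adjusting for enrolment CFQ would lower the SE by about 5% to 13%. That assumes r between 0.3 and 0.5 and many shifts per subject. The direction is secure; the size is not, since the article gives neither r, the ICC nor the number of shifts. With few shifts per subject the gain is smaller, and for a slope contrast it is close to nil.

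**What to change.** Prespecify the enrolment CFQ score as a fixed effect in the end-of-shift fatigue model, and keep the unadjusted model as a sensitivity analysis. Scheduled shift length may be added as a second covariate, taken from the calendar as first registered at enrolment and not from later edits, with a smaller expected gain. Do not adjust for start-of-shift ratings.

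The article reports enrolment closed and follow-up under way, so the change is still possible if it is fixed before outcomes are examined by arm. It needs no new data and costs one or two degrees of freedom. The gain may prove modest, because CFQ and the outcome are different instruments.

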In this paper, we present the study protocol for a controlled 90-day pilot trial with an assessment-only control group. This study has two objectives. First, we aim to determine the performance characteristics of a text messaging tool as the prime vehicle for delivery of a sleep and fatigue intervention for EMS shift workers. Second, we aim to determine if a short message service (SMS) program with tailored intervention messages is effective at reducing perceived sleepiness and/or fatigue among emergency medicine clinician shift workers. Additional aims include testing whether a theory-based behavioral intervention, delivered by SMS, changes any one of eight factors that are hypothesized to impact ‘alertness behaviors’. These factors are based on the Integrative Model of Behavioral Prediction and include: 1) attitudes, 2) perceived norms, 3) self-efficacy, 4) knowledge, 5) salience, 6) habits, 7) environmental constraints, and 8) behavioral intent. We hypothesize that performance (study subject compliance) with text message assessments will be high and that our SMS behavioral intervention distributed via text messaging will show a reduction in perceived fatigue at the end of shiftwork. We hypothesize that our intervention will impact one or more of the eight factors predictive of alertness behaviors. Study findings will provide important preliminary data to address key questions related to the feasibility and performance of an SMS platform to address sleep and fatigue among shift workers.

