## Methods/Design

### Trial design

The SleepTrackTXT study is a single center, two-arm, parallel, single blind, randomized controlled trial. We use a study webpage as our main means of recruitment. Eligible participants contact the study team to request enrollment and undergo screening. We will randomize 100 emergency workers to one of two groups (N = 50 each). The intervention group will receive 90 days of automated SMS (text messaging) dialogue via a computer. Messages to the subjects will include questions on perceived sleepiness, fatigue, difficulty with concentration, work-related injury at the start, during, and end of scheduled shifts. If subjects in the intervention arm report a high level of sleepiness or fatigue at the beginning of or during their shift the computer recommends one of four evidence-based strategies for improving alertness and reducing sleepiness or fatigue during their shiftwork. The control group subjects will participate in a 90-day SMS dialogue with the computer. In this group, the computer will ask at the start, during, and end of shifts about sleepiness, fatigue, difficulty with concentration, and work-related injury, but the computer will make no recommendations to improve alertness and reduce sleepiness or fatigue. The details of this study design are described below in accordance with the CONSORT statement. Figure 1 provides a visual illustration and flow chart of the SleepTrackTXT trial. This study was approved by the University of Pittsburgh Institutional Review Board and is registered at clinicaltrials.gov (registration number: NCT02063737). All subjects are required to give informed consent.

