Work-related fatigue and recovery will be measured with the Occupational Fatigue Exhaustion/Recovery Scale (OFER) [38]. The OFER is a reliable and valid 15-item scale that measures acute fatigue, chronic fatigue, and inter-shift recovery. Higher OFER scores ( ≥80) indicate higher fatigue and greater ability to recover between shifts. At baseline and at 90-days follow-up we will measure a participant’s behavior and intention to engage in behaviors that improve alertness with the Sleep, Fatigue, & Alertness Behavior Survey (SFAB). We developed the SFAB based on the Integrated Model of Behavioral Prediction [34]. The SFAB is comprised of 83 candidate items intended to measure eight factors and domains considered to be predictive of behavioral intent to improve alertness during shiftwork. These eight domains include: 1) attitudes about improving or maintaining alertness on duty; 2) perceived norms regarding what the person or others (peers) think or feel about being sleepy or fatigued while at work; 3) self-efficacy regarding improving or maintaining alertness while on duty; 4) knowledge of behaviors for improving or maintaining alertness on duty; 5) salience (perceived importance) of specific alertness behaviors; 6) habits linked to sleepiness, fatigue, and alertness; 7) environmental constraints to performing specific alertness promoting behaviors; and 8) intention to perform one or more behaviors. We will administer the SFAB at baseline and at 90-days follow-up to categorize individuals into one of four behavioral categories and assess the following changes in behavior: 1) intention to reduce fatigue and sleepiness on duty and reports consistent use of alertness-promoting behaviors; 2) intention to reduce fatigue and sleepiness on duty and reports inconsistent or no use of alertness-promoting behaviors; 3) no intention to reduce fatigue or sleepiness on duty and reports consistent use of alertness-promoting behaviors; and 4) no intention to reduce fatigue or sleepiness on duty and reports inconsistent or no use of alertness-promoting behavior.

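### The between-arm tests of the eight SFAB scales leave out the baseline score; adjusting for it would give a more precise comparison at no cost

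*Protocol article*

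**What the plan says.** The Background section sets the question as an effect of the intervention: "Additional aims include testing whether a theory-based behavioral intervention, delivered by SMS, changes any one of eight factors" thought to influence alertness behaviour. The data for it come from two administrations. Participant level measures says: "We will administer the SFAB at baseline and at 90-days follow-up". Table 1 and Follow-up measures agree, and Statistical analysis repeats it: "The eight scale components of the SFAB survey are measured at baseline and at the end of the study". The scoring is continuous: "Likert responses will be scored as continuous measures and weighted from 0 to 100, with higher scores indicating more positive scores".

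The analysis of these scales is then given in one sentence, "We will test for changes over time and between-group differences in these scales using one sample and two sample t-tests", with a fallback: "If the data are highly skewed we will use non-parametric tests including the sign rank test and Mann-Whitney U test". The general rule is: "All statistical testing will be two-sided with alpha set at <0.05".

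Three things are left open. The text does not say whether the two-sample test compares 90-day scores or changes from baseline. It does not say whether the one-sample test is run in each arm or in all subjects together. It does not say which of the two tests answers the aim in the Background.

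**The concern.** The baseline SFAB score is collected in both arms before any message is sent, and the same instrument is likely to predict the 90-day score. A two-sample test on 90-day scores makes no use of it. A two-sample test on change scores uses it with a fixed coefficient of one, which is too large unless the correlation is very high. Both leave avoidable noise in the comparison. With 50 subjects per arm (Trial design), that affects whether a moderate shift in any scale can be seen.

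There is a smaller point of clarity. The one-sample test of change stands beside the between-group test without a stated role. Both arms answer a long survey twice and receive questions about sleepiness and fatigue for 90 days, so scores may move in both arms for reasons unrelated to the recommendations. A one-sample test cannot separate such movement from an intervention effect.

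**Working it through.** **The plan's own power figure.** The only one is in Sample size: 80% power at 25 per arm for a difference of 0.78 in end-of-shift fatigue, by Mann-Whitney U with a logistic distribution. It reproduces: noncentral-t power with n multiplied by π²/9 = 1.097 gives 80.9%, and 20,000 simulated trials give 79.1%. It concerns a different outcome and does not bear on the SFAB, for which no power is stated.

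**Inputs.** From the document: 50 per arm, two-sided alpha 0.05, SFAB at baseline and 90 days, scores treated as continuous. Assumed, because the document gives neither an SFAB standard deviation nor a correlation: equal SD at both times, a linear relation, r from 0.3 to 0.8, and differences expressed in SD units of a single score.

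**Variance of the between-arm contrast**, relative to a test on 90-day scores:

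- 90-day score: 1
- change score: 2(1 − r)
- ANCOVA: 1 − r²

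So ANCOVA relative to the 90-day-score test is 1 − r². Relative to the change-score test it is (1 − r²) / [2(1 − r)] = (1 + r)/2. At r = 0.5 these are 1 − 0.25 = 0.75 and 1.5/2 = 0.75.

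**Power.** With relative variance v and true difference d, the noncentrality is d·√(n/2)/√v, referred to t on 98 degrees of freedom (the one degree lost to the covariate is ignored). For n = 50, d = 0.5 and r = 0.5:

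- either unadjusted test: 0.5 × 5 / 1 = 2.50, power 69.7%
- ANCOVA: 0.5 × 5 / √0.75 = 2.89, power 81.6%

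Results with 50 per arm, each cell in the order 90-day score / change score / ANCOVA:

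| r | Relative variance | Difference detectable with 80% power (SD) | Power for 0.5 SD |
|---|---|---|---|
| 0.3 | 1 / 1.40 / 0.91 | 0.57 / 0.67 / 0.54 | 70% / 55% / 74% |
| 0.5 | 1 / 1.00 / 0.75 | 0.57 / 0.57 / 0.49 | 70% / 70% / 82% |
| 0.7 | 1 / 0.60 / 0.51 | 0.57 / 0.44 / 0.40 | 70% / 89% / 93% |
| 0.8 | 1 / 0.40 / 0.36 | 0.57 / 0.36 / 0.34 | 70% / 98% / 99% |

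At r = 0.5 the gain equals that of raising the arms from 50 to 50/0.75 ≈ 67 subjects. If only 40 per arm completed the 90-day survey, power at r = 0.5 would go from 60% to 72%. Below r = 0.5 the change-score test is the worse of the two unadjusted tests, and above it the 90-day-score test is. ANCOVA is ahead of both in every row.

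**Change common to both arms.** Suppose there is no intervention effect and both arms shift by 0.2 or 0.3 SD of the change score. A one-sample test in one arm of 50 (noncentrality 0.2 × √50 = 1.41 or 0.3 × √50 = 2.12) is significant 28% or 55% of the time. The planned two-sample test stays at 5%, because the common shift cancels in the contrast.

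**The case against.** A reader might infer that the plan will judge the intervention by within-arm significance, and that ANCOVA is needed to stop drift being taken for an effect. The document does not support either step. It names two questions, change over time and difference between groups, each with its own test, and never says that a one-sample result will be read as the intervention effect or that it will be run by arm. The 28% and 55% above are correct detections of a real change over time, not error rates of the planned between-group comparison. Protection against common change comes from the randomised contrast, which the two-sample test already provides; a baseline covariate adds nothing to it. What stands on the other side is only that the role of the one-sample tests is unstated, and a label settles that.

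It can also be said that the gain is uncertain. That is right: r is unknown, and the saving in variance is only 9% against 90-day scores at r = 0.3 and 15% against change scores at r = 0.7. But the uncertainty is also a reason to adjust, since which unadjusted test does worse depends on r.

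Third, an article leaves much to a full analysis plan. Here, though, the article names a specific method, so a better one can fairly be proposed. Finally, the fallback for skewed data is announced in advance, and preferring robust intervals to rank tests is largely a matter of taste.

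**Conclusion.** The point holds as one of efficiency. The planned between-arm tests of the SFAB scales are valid under randomisation but do not make the best use of a baseline score that every subject is due to provide. Across assumed correlations of 0.3 to 0.7, adjustment reduces the variance by 15% to 35% against change scores and by 9% to 49% against 90-day scores. The result rests on equal SDs at the two times, a linear relation, a correlation that the document does not give, and 50 completers per arm. The SFAB is an additional aim of a pilot. It is neither the primary intervention outcome nor the basis of the sample size, so the consequence is limited. The claim that the analysis is invalid, or open to drift in its between-group test, does not hold.

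**What to change.** In Statistical analysis, replace the two-sample test of each SFAB scale with a linear regression of the 90-day score on arm and baseline score. Report the adjusted between-arm difference with its 95% CI, and state that this is the test of the SFAB aim given in the Background. Keep the one-sample tests of change if wanted, but label them descriptive and say whether they are by arm or pooled. A rank-based or robust version of the adjusted comparison may be kept for skewed scores.

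The cost is a few sentences of analysis wording. No further data or subjects are needed. Trial status reports that follow-up data were still being collected when the article was accepted, so at that point the change could still be written down before the 90-day data were complete.
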